5.6 PATIENT POPULATION

Potential participants are patients with chronic nephropathy treated in Nephrology Department, Copenhagen County Hospital in Herlev. The Patients are contacted in connection with a visit to the department and informed about the project. Interested patients meeting inclusion and exclusion criteria are included in the project. No fee is paid to study participants.

A total of 60 patients are scheduled to participate: 20 patients with prior ACE-I therapy, 20 patients with prior AIIA therapy and 20 patients without prior treatment with either ACE-I or AIIA at the entry of the study.

5.7 INCLUSION CRITERIA

The patient can be included in the project if the answer is YES to the following:
- Age between 18 and 75 years
- Have submitted voluntary written informed consent
- Have plasma creatinine between 150-350 µmol/l
- Systolic blood pressure> 110 mmHg
- Negative pregnancy test in fertile women

5.8 EXCLUSION CRITERIA

The patient may not be included in the project if the answer is YES to at least one of the following:
- Treatment with both ACE-I and A-II-A at inclusion time
- Pregnancy or lactation
- Treatment with immunosuppressive, steroids or NSAIDs
- Severe chronic heart failure (NYHA III-IV)
- Chronic liver disease
- Suspected or confirmed renal artery stenosis
- Cardiac arrhythmia and / or implantable pacemaker
- AMI or cerebrovascular event within the last 3 months
- Allergy to ACE-I or AIIA
- Amputation of a limb or crural or femural amputation.
- Dementia or a mental condition that prevents understanding of study requirements
- Dialysis or transplantation
- Treatment with aldosterone antagonists
- Plasma-potassium> 5.5 mmol/l
- Other severe chronic non-renal disease

5.9 CRITERIA FOR WITHDRAWAL

Study participants will be excluded from the trial if the following conditions occur:

- Pregnancy
- Adjacent to other serious illness
- Unacceptable side effects such as angioneurotic edema
- Intractable hyperkalemia
- Cardiovascular event such as AMI or cerebral apoplexia
- Increase in p-creatinine of> 30% from baseline
- Request from the study participant concerning exclusion

Decision on the withdrawal of the study participant from the trial can be carried out by the investigator, the clinical supervisor and the two co-supervisors.

5.10 DEMOGRAFIS KE VARIABLE

The following is recorded for each patient: sex, age, weight, height, blood pressure, heart rate, Cr-EDTA clearance, renal diagnosis, date of diagnosis, if any other diagnoses, habitual medication, daily tobacco consumption. A case report form will be prepared for each patient comprehensive registration form for demographic and paraclinical variables (Annex IV-VI) and data from applanationtonometry measurements. Data will be regularly entered for statistical analysis using the computer. The patient's name and Social Security number will not be entered, but the patient will be assigned a number in chronological order.

5.11 PARACLINICAL VARIABLE

The gained data is processed in the apparatus via a mathematical analysis to characterize the pulse wave and pulse wave velocity.
The following blood samples are taken at baseline and at all pulse wave measurements on all patients: b-hemoglobin, b-leukocytes, b-platelets, p-bilirubin, p-ALT, p-alkaline phosphatase, hsC-reactive protein, p-creatinine, p- urea, p-sodium, p-potassium, p-bicarbonate, glucose, p-albumin, p-cholesterol, p-triglyceride, p-HDL, p-LDL, p-urate, p-parathyroid hormone and p-homocysteine.

The following blood samples are taken at each clinical control: b-hemoglobin, p-creatinine, p-BUN, p-albumin, p-potassium and sodium.

*For blood samples:*At each blood sample a total of 30-40 ml of blood is taken. The blood will be analyzed immediately in connection with the measurement. An extra glass of blood will be taken in case of the need of reanalysis of samples.

*24 h urine collection*:
At baseline and at each measurement a 24 h urine collection ís delivered for analysis of urinary albumin and urinary sodium. The urine will be analyzed immediately in connection with the investigation. An extra glass of urine will be taken in case of the need of reanalysis of the sample. A pregnancy test in fertile women will be performed on a urine sample prior to entry into the study.

*Chromium-EDTA clearance*:
The estimated GFR <20 ml/min: 24h clearance with blood 5 and 24 hours after injection of 3.5 MBq of 51-Cr-EDTA.
The estimated GFR> 20 ml/min: blood sampling after 180, 200, 220 and 240 min. after injection of 3.5 MBq 51-CR-EDTA.

*Procedure regarding data at project completion*
All data will be stored for a maximum of 15 years, after which they will be destroyed. Data is stored in Nephrology Section B, KAS Herlev, and among the members of the project group. Data will only be available to the project group.

5.12 PRACTICAL PERFORMANCE

Patients who are interested in participating in the study are informed about the project. The written patient information (Annex IA, IB and III) obtained and reviewed and a possibly. consent is issued.

A time schedule is agreed for Chromium-EDTA clearance, the measurements and the clinical controls.

Demographic data is recorded, possibly using the patient record.

*Randomization*Prior treatment with ACE-I/AIIA: Randomization is done by drawing lots from a bag in which there are 40 notes. Half of these are inflicted ACE-I treatment and the other half is applied AIIA therapy. Randomization for the group of patients without prior ACE-I/AIIA is done in the same way by lot from a bag, half of the 20 notes bearing the ACE-I in the first period and AIIA in the second period and the other half is applied AIIA in the first period, and ACE-I in the second period. The result of the randomization is recorded in the patient's Case Report Form.

*Measurement I-VI*The day before the measurements the patient collects urine in a dunk.
At the day of the first measurement the patient does not take his usual medications until after the measurement. In case of diabetes, the habitual diabetes medication is taken as usual, but all other medications are taken after the measurement. At the other measurements the study medication is taken 2 hours before meeting time, but all other medications taken after the measurement, except from antidiabetic medication. On arrival the patient is weighed. The patient brings 24 h urine collection.

At study start (baseline) blood sampling is taken in a peripheral vein for analysis of: b-hemoglobin, b-leukocytes, b-platelets, p-bilirubin, p-ALT, p-alkaline phosphatase, hsC-reactive protein, p-creatinine , p-urea, p-sodium, p-potassium, p-bicarbonate, glucose, p-albumin, p-cholesterol, p-triglyceride, p-urate, p-parathyroid hormone and p-homocysteine.

At the other measurements and clinical controls the following blood samples are taken for analysis: b-hemoglobin, p-creatinine, p-urea, p-albumin, p-potassium and p-sodium.

The patient is placed supine on a bed in a quiet room and is resting for 15 minutes. A blood pressure is recorded by a mercury sphygmomanometer.

Data is recorded in the schedules attached as Annex IIA and IIB.

*Clinical controls*
Every 2^nd^ to 3^rd^ week the patient meets for blood pressure control and control of therapy. Blood sampling is carried out as described above. Study medication is adjusted.

*Chromium-EDTA clearance*There is a total of 2 study days for each patient on the department of clinical physiology, where the patient has a Cr-EDTA clearance performed. The days lies immediately before study start and after the termination of the study.
Intravenously injected 51 Cr-EDTA is excreted exclusively by glomerular filtration. Measurement of plasma concentration in one or more blood samples therefore allows calculation of the glomerular filtration rate.
At an estimated GFR <20 ml/min: 24 h clearance with blood sampling 5 and 24 hours after injection of 3.5 MBq of 51-Cr-EDTA.
At an estimated GFR> 20 ml/min: blood sampling after 180, 200, 220 and 240 min. after injection of 3.5 MBq 51-CR-EDTA.

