5.5 DESIGN

Open randomized crossover trial in patients with non-dialysis chronic renal failure study:

• The effect of treatment with either ACE-I or AIIA on parameters of arterial stiffness assessed by the applanationtonometry method.
• The effect of treatment with both ACE-I and AIIA on parameters of arterial stiffness assessed by the applanationtonometry method.

The patient population is divided into 2 groups: one group with prior treatment with either ACE-I or AIIA (group I) and another group without prior treatment with either ACE-I or AIIA (group II). The study medication is as follows: the ACE inhibitor Enalapril and angiotensin receptor antagonist Candesartan. The study extends over three periods of 8 weeks. Patients in group I are randomized to receive either Enalapril in both the first and second periods or Candesartan in both the first and second periods. Patients in group II is randomized to either treatment with Enalapril or candesartan in the first period with a shift to the opposite drug in the second period.
Common to both groups is a double treatment with both Enalaprilat and Candesartan in the third period.
There will be carried out measurements at baseline and after the first, second and third period. Each study includes measurement by the applanationtonometry method where the tonometry is placed with gentle pressure towards the skin above the radial artery , thereby providing data for pulse wave analysis. Subsequently, measurements are performed equivalent to the radial, carotid and femoral arteries, thereby providing data for pulse wave velocity determination. The study design is shown in flow diagrams attached as Annex Ia + b.
There must be delivered 24 h urine collection before baseline and after every period. Chromium-EDTA clearance is carried out before and at the last visit in the trial.

*Patients receiving ACE-I or AIIA therapy prior to the trial.*
Pulse wave measurements are carried out at baseline and after each treatment period of 8 weeks, a total of 4 times. In addition comes 6 clinical control sessions and two appearances for the making of Chromium-EDTA clearance before and after the project.

Measurement I (start)

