• At the first day of the study the patient meets fasting from midnight and without smoking, but with permission to drink water. Alcohol should not be taken for 24 hours before study start. The patient waits to take his medication until after the study. For patients with diabetes, however, a light breakfast is consumed at home and the usual medications for diabetes, all medicines taken after the study. Investigations commenced approx. at. 9:00 after blood sampling and then 15 min. rest in supine position. The studies are carried out in a quiet room with ambient temperature 20-22 degrees. A total of 2 measurements are carried out by the same investigator.
After the measurement the patient's habitual ACE-I or AIIA therapy is discontinued and patients are randomized to a scenario with either Enalapril in the first and second periods (ACE-I group) or treatment with Candesartan in the first and second period (AIIA group). Common to both randomization groups is a common dual blockade with both Enalapril and Candesartan in the third period.
The ACE-I group is started in tablet Enalapril 5 mg daily and is given tablets until the next appointment. AIIA group is started in tablet Candesartan 4 mg daily and are given tablets until next appointment. For women of childbearing age, the drugs will only be supplied in case of a negative pregnancy test.

The patient must before start of treatment have had a Chromium-EDTA clearance performed as well as a 24 h urine collection, which is attempted planned for the day of measurement I.

Adjustment of medicine and clinical control Ia (after 2-3 weeks)
• Attendance in the morning for blood pressure measurement and blood sampling. Control of treatment. The AIIA-group is increased to a tablet of candesartan 8 mg daily and the ACE-I group is increased to a tablet Enalapril10 mg daily. Both groups were handed out tablets for next appointment.

Adjustment of medicine and clinical control Ib (after 5-6 weeks weeks)
• Attendance in the morning for blood pressure measurement and blood sampling. Control of treatment. The AIIA group increased to a tablet of candesartan 16 mg daily and the ACE-I group increased to a tablet Enalapril 20 mg daily. Both groups were handed out tablets for next appointment.

Measurement II (after approx. 8 weeks, 1^st^ period)

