7.3 SUMMARY

The study patient population is a high risk group in terms of primarily cardiovascular morbidity and mortality. Based on several clinical controlled studies, blocking of the renin-angiotensin system have been shown to reduce this morbidity and mortality. Two of the three patient groups in the project will already be in treatment with either ACE-I or AIIA prior to the start of the study.
To minimize the risks of treatment, the patient population is carefully selected based on inclusion and exclusion criteria. Furthermore, there are frequent clinical and paraclinical control of the treatment in order to, at an early stage, observe any side effects or complications from the treatment. Finally, patients have the opportunity to contact a Nephrology doctor 24 hours a day if questions arise. Recording and reporting of adverse events follow applicable laws.

To sum, the advantages and disadvantages for the overall study group are assessed to balance.

The project will not be started until approval from the regional ethical committee, the Data Protection Agency and the Medicines Authority is obtained.
No trial participant will be included in the project before he has made a voluntary, written informed consent.
Patients who do not wish to participate in the project would not require justification, and the patient's participation or not should not affect the further monitoring or treatment of the patient.

The study is carried out in accordance with the Helsinki Declaration.

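### Group I is recruited as 20 prior-ACE-I and 20 prior-AIIA patients but drawn from one bag of 40, so prior drug can be unbalanced by chance between the enalapril and candesartan arms

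*Protocol*

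**What the plan says.** Section 5.6 plans 60 patients: "20 patients with prior ACE-I therapy, 20 patients with prior AIIA therapy and 20 patients without prior treatment with either ACE-I or AIIA". Section 7.3 also counts by prior drug: "Two of the three patient groups in the project will already be in treatment with either ACE-I or AIIA prior to the start".

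Section 5.5 merges the two pre-treated groups into Group I, and section 5.12 allocates Group I in a single draw: "Randomization is done by drawing lots from a bag in which there are 40 notes". On the contents of the bag it says: "Half of these are inflicted ACE-I treatment and the other half is applied AIIA therapy". Patients without prior treatment (Group II) have their own bag, with "half of the 20 notes bearing the ACE-I in the first period and AIIA in the second period" and the other half in the reverse order. Allocation is thus stratified by whether a patient was pre-treated, but not by which drug.

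Two further statements in section 5.5 matter. Group I does not cross over between the single drugs: "Patients in group I are randomized to receive either Enalapril in both the first and second periods or Candesartan in both the first and second". And baseline comes before the change of treatment: "After the measurement the patient's habitual ACE-I or AIIA therapy is discontinued and patients are randomized". No washout is described. Section 5.1 lists the comparison of the two single drugs as an additional aim.

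**The concern.** The plan recruits to a quota on prior drug and then ignores that factor at allocation. In Group I, enalapril versus candesartan is compared between patients, so a difference between the arms in prior drug does not cancel as it would in a crossover.

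Prior drug could matter because Measurement I is made on a patient established on the habitual drug. If PWV differs between patients established on an ACE inhibitor and those established on an angiotensin antagonist, change from baseline carries that difference. An arm with more patients from one prior-drug group carries more of it. At stake is the precision and credibility of the Group I single-drug comparison.

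**Working it through.** **The plan's own figure.** The protocol gives no figure for balance. Its only related figure is in section 5.14: power 0.82 (brachial, SD 1.1 m/s) and 0.99 (aortic, SD 0.75 m/s) at n = 20 for a difference of 1 m/s. With 20 per arm, two-sided 5% and the normal approximation:

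- brachial: 1 / (1.1 × √(2/20)) − 1.96 = 0.915, power 0.820
- aortic: 1 / (0.75 × √(2/20)) − 1.96 = 2.256, power 0.988

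Both are reproduced. They depend on arm size only, so any fix that keeps 20/20 leaves them unchanged.

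**Chance of imbalance.** Inputs: 20 prior-ACE-I and 20 prior-AIIA patients (5.6); 20 ACE-I and 20 AIIA notes in one bag (5.12). Let X be the number of prior-ACE-I patients who draw enalapril. When the bag is used up, X is hypergeometric:

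P(X = k) = C(20,k) × C(20,20−k) / C(40,20)

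The mean is 10, the variance 20 × 0.5 × 0.5 × 20/39 = 2.564, and the SD 1.60.

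| Split of a prior-drug group between arms | Probability |
|---|---|
| exactly 10:10 | 0.248 |
| 11:9 or worse | 1 − 0.248 = 0.752 |
| 12:8 or worse | 0.343 |
| 13:7 or worse | 0.113 |
| 14:6 or worse | 0.026 |
| 15:5 or worse | 0.004 |

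**Effect on the comparison.** Let g be the difference in mean PWV change between the prior-drug groups. The enalapril arm holds X/20 prior-ACE-I patients and the candesartan arm (20 − X)/20. The unadjusted contrast therefore shifts by g × (2X − 20)/20. At 13:7 this is g × 6/20 = 0.30g. The protocol gives no value for g, so these are assumptions:

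| Assumed g (m/s) | Shift at 13:7 (m/s) | SD of shift over all draws = g × 1.60 × 2/20 (m/s) |
|---|---|---|
| 0.25 | 0.075 | 0.04 |
| 0.5 | 0.15 | 0.08 |
| 1.0 | 0.30 | 0.16 |

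**How g could arise.** Suppose PWV on enalapril exceeds PWV on candesartan by d, each prior drug acts like the study drug of its class, and change from baseline is analysed. Continuers then change by 0, switchers to candesartan by −d and switchers to enalapril by +d. The arm difference is 2d × (20 − X)/20, which is d at X = 10, 0.7d at X = 13 and 1.3d at X = 7.

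**Staying in class versus switching.**

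- Enalapril arm: X prior-ACE-I patients stay in class; 20 − X prior-AIIA patients switch.
- Candesartan arm: 20 − X prior-ACE-I patients switch; 20 − (20 − X) = X prior-AIIA patients stay in class.

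Both arms hold X patients who stay and 20 − X who switch, whatever X is. At 13:7 it is 13 and 7 in each arm.

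**The case against.** A reader might infer that one arm could hold mostly patients staying in their class and the other mostly switchers, so that the drug comparison is confounded with continuing versus switching. The protocol's numbers do not support this. With 20/20 prior-drug quotas and 20/20 notes, that share is identical in the two arms for every possible draw. It could differ only if recruitment stopped short or if replacements (5.14) disturbed the totals. Nor does the protocol name prior drug as a modifier of response.

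Other points on the plan's side:

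- **The draw is fair.** Over repeated randomisation the comparison is unbiased, and 14:6 or worse has a chance of only 2.6%. This stands.
- **The prior-drug effect may be nil.** Section 5.1 expects ACE inhibitor and angiotensin antagonist to have equal effect. If so, and the prior-drug groups are otherwise alike, g is zero and nothing shifts. This stands as a limit on size, but the comparison exists to test that expectation.
- **Adjustment is available.** Habitual medication is recorded (5.10), and a SAP not shown may include prior drug. At 13:7 the variance factor within a prior-drug group is 1/13 + 1/7 = 0.220 against 0.200 at 10:10, so the adjusted standard error rises by about 5% (√(0.220/0.200) = 1.05). This largely answers the concern if adjustment is planned, but a SAP cannot change the allocation itself.
- **The scope is narrow.** The main hypothesis, dual versus single blockade, is assessed within patients, and Group II has its own bag and crosses over. This stands.

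**Conclusion.** The point holds as a modest design weakness. The protocol recruits Group I to quotas on prior drug but does not use prior drug in the draw, which leaves a 34% chance of a 12:8 or worse split and an 11% chance of 13:7 or worse. At 13:7, 0.30 of any prior-drug difference in PWV change enters the unadjusted Group I contrast: 0.075 to 0.30 m/s for assumed differences of 0.25 to 1.0 m/s, against the relevant difference of 1 m/s.

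This rests on three assumptions: the 20/20 quotas are met and the bag is used up; the comparison is unadjusted for prior drug; and g, which the documents do not give, is not zero. The baseline mechanism applies to an analysis of change from baseline. For on-treatment values, the same 0.30 applies to whatever difference exists between the prior-drug groups in those values.

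**What to change.** In section 5.12, replace the bag of 40 with two bags of 20 notes, each with 10 ACE-I and 10 AIIA notes, one for each prior-drug group. Leave the Group II bag as it is. Include prior drug as a factor in the Group I comparison, in the protocol or the SAP. Once both bags are used up, each arm holds exactly 10 patients from each prior-drug group, and the chance of any imbalance falls from 75% to zero.

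The cost is one extra bag and one sentence. Arm sizes stay 20/20 and the stated power is unchanged, with no added patients or visits. The drawback is that the last draws from a smaller bag are slightly more predictable, which matters a little in an open trial.

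Section 5.12 has no rule for allocating replacements of withdrawn patients. Exact balance is therefore assured only for the first 40 drawn, and the same sentence could state how replacements are allocated. If drawing has already begun, adjustment for prior drug alone recovers most of the benefit.

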5.13 STUDY MEDICATION

The study medication is the tablet Enalapril, an ACE inhibitor and the tablet Candesartan, which is an angiotensin receptor antagonist. Both drugs are approved drugs with existing SPC approved by the Medicines Agency. These will be available at the place of study, when the experiment is initiated. There is not decided any particular importer/manufacturer of this medication for this study.
Full treatment dose, respectively. Enalapril 20 mg and 16 mg candesartan once daily is the recommended maximum dose according Medicines catalog. Maximum dose is achieved as recommended after a titration period of 5-6 weeks. For combination treatment with both drugs, the study participant will already be in full dose treatment with one drug but will then slowly be uptitrated to full treatment dose of the other drug over 5-6 weeks. Dosing, route of administration, dosing frequency, titration and treatment period, are according to standard practice.
After the termination of the study period or withdrawal of the study, the participant returns to his usual medications.

The medicine will be delivered through Copenhagen County Central Pharmacy in ordinary medicine boxes. The medicine will be counted and packed by the investigator to each study participant for the scheduled period. Any handed medication will be recorded in the patient's Case Report Form, as well as any returned medication. There will also be taken account of receiving medication. The subjects will be thoroughly informed about the importance of taking the medication and that accounts will be kept with the medication for each patient. The frequent appearances of the patients are further helping to ensure a high patient compliance.

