Recording and reporting of adverse events follow applicable laws. Referenced in the following text to the *Order of clinical trials of drugs in humans* defined types of side effect. Unexpected and serious suspected adverse reactions (Suspected Unexpected Serious Adverse Reactions, SUSAR) that are either fatal or life threatening will be reported to the Medicines Agency no later than 7 days after the sponsor-investigator has knowledge of them, and no later than 8 days after notification, the sponsor Investigators announce Medicines Agency all relevant information on follow-up. All other unexpected serious adverse reactions, will also be reported to the Medicines Agency no later than 15 days after the sponsor-investigator has knowledge of these. Serious, suspected adverse reactions (Serious adverse reaction, SAR) will be reported annually to the Medicines Authority. Serious adverse events and serious adverse events (Serious Adverse Events, SAEs) will be reported annually to the Scientific Ethical Committee. Adverse events and side effects will appear in the final report to the Medicines Authority of the study results.

If intolerable adverse effects, the participant will be withdrawn from the trial. The patient will then return to his usual medications and follow-up in the department of Nephrology, as long as required.

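### The exit rule returns every withdrawn participant to usual medication, with no exception for Group I patients withdrawn for pregnancy or angioneurotic edema

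*Protocol*

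**What the plan says.** The general exit rule is in Protocol section 5.13: "After the termination of the study period or withdrawal of the study, the participant returns to his usual medications". Section 7.2 covers withdrawal for intolerable adverse effects and gives the same destination, adding follow-up: "The patient will then return to his usual medications and follow-up in the department of Nephrology, as long as required".

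What usual medication means depends on the stratum. For patients already on one of the two classes (Group I), section 5.5 says at Measurement I: "After the measurement the patient's habitual ACE-I or AIIA therapy is discontinued". Section 5.6 plans "20 patients with prior ACE-I therapy, 20 patients with prior AIIA therapy" and a further 20 patients on neither class (Group II).

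Section 5.9 lists the reasons for withdrawal. Pregnancy comes first, and the list includes "Unacceptable side effects such as angioneurotic edema". The adverse-effect text in section 7.2 names angioneurotic edema under ACE-I and not under AIIA.

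On pregnancy the protocol is careful elsewhere. Section 5.8 excludes "Pregnancy or lactation". Section 5.5 adds: "For women of childbearing age, the drugs will only be supplied in case of a negative pregnancy test". Section 7.2 requires effective contraception during the study and for one week after it, a span justified as five plasma half-lives of the medication.

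**The concern.** The exit rule is written as a single outcome for all exits. Two of the listed reasons for withdrawal are ones where going back to the habitual drug is the wrong result.

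- **Pregnancy.** The protocol keeps these drugs away from pregnant women at entry and at first supply, and its contraception rule extends past the last dose. The exit rule then puts a Group I woman who becomes pregnant back on a drug from the same two classes.
- **Angioneurotic edema.** A patient with prior ACE-I therapy withdrawn for this event goes back to the class under which the protocol lists it.

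What is at stake is the safety of a small number of patients, and whether the text can be followed as written. No estimate or test in the trial depends on it.

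**Working it through.** The protocol gives no figure to reproduce. The check is to follow the exit rule through each combination of prior therapy and reason for withdrawal.

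**Inputs**
- Rule: return to usual medication at completion or withdrawal (5.13), repeated for intolerable adverse effects (7.2).
- Usual medication: Group I includes an ACE-I or an AIIA, and Group II includes neither (5.5, 5.6).
- Reasons for withdrawal: section 5.9.
- The protocol's position on each reason: sections 5.5, 5.8 and 7.2.

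**Step 1. Who has a drug of these classes to resume?** Group I = 20 prior ACE-I + 20 prior AIIA = 40 of the 60 planned. Group II = 60 − 40 = 20, with neither class, so the rule restarts nothing there.

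**Step 2. What the rule does, read literally**

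| Prior therapy | Withdrawn for pregnancy | Withdrawn for angioneurotic edema |
|---|---|---|
| ACE-I (20 planned) | ACE-I resumed: conflicts with the pregnancy safeguards | ACE-I resumed: the class under which the event is listed |
| AIIA (20 planned) | AIIA resumed: conflicts with the pregnancy safeguards | AIIA resumed: the event is not listed for this class, so no conflict on the text |
| Neither (20 planned) | Neither class resumed | Neither class resumed |

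**Step 3. Does the randomised drug change this?** Group I patients are randomised to enalapril or candesartan for periods 1 and 2, and for period 3 section 5.5 says: "Common to both randomization groups is a common dual blockade with both Enalapril and Candesartan in the third period". The exit rule points to the habitual drug and not to the trial drug, so the table holds whichever drug was being taken at withdrawal.

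**Step 4. Is there an exception anywhere?** Section 5.9 says who may decide on withdrawal but not who decides on resuming the habitual drug. Section 7.2 places the return to usual medication and the nephrology follow-up side by side, without making the first wait for the second. The instructions at Measurement IV in section 5.5 cover completion only. Section 7.3 gives 24-hour access to a nephrology doctor but no rule on resumption. The patient information in Appendix II is not available for this review.

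**Step 5. How many patients?** For angioneurotic edema the ceiling is the 20 planned patients with prior ACE-I therapy. For pregnancy it is the women of childbearing age within Group I, a number the protocol does not give. Expected withdrawals for either reason are not given either.

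**The case against.** The strongest reply is that the sentence in 5.13 hands the patient back to ordinary care and is not a prescribing order. No nephrologist would read it as telling them to give an ACE-I to a pregnant woman. Section 7.2 provides nephrology follow-up for as long as needed, section 7.3 gives round-the-clock access to a nephrology doctor, and section 5.13 relies on approved product information. This stands as a reason to expect little harm. It does not alter a rule that is stated twice without a condition.

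A second reply is that the pregnancy safeguards are written for trial entry and study-drug supply, not for habitual prescribing after exit, and that required contraception makes the case rare. Both parts are true. But the habitual drugs belong to the same two classes, and the protocol gives no reason to treat them differently in pregnancy.

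A third is that the only contraindications stated in section 7.2 are renal artery stenosis and allergy. That is correct. A reader might infer that the exit rule breaches the allergy criterion, but the protocol never calls angioneurotic edema an allergy. The point is narrower: the rule restarts the class whose listed adverse effect ended participation. That this should be avoided is a clinical judgement, which the protocol does not state as a rule.

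Three further inferences go too far:

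- *That returning to usual medication is also wrong after hyperkalemia or a creatinine rise above 30%.* Going back to one habitual drug may be a step down from dual blockade, and section 7.2 provides nephrology follow-up after intolerable adverse effects.
- *That both classes should be barred after angioneurotic edema on candesartan or on dual therapy.* The protocol does not list the event as an AIIA effect.
- *That the problem is as large as Group I.* The 40 patients include men and women past childbearing age (the age range is 18 to 75), so the count says little about how many the pregnancy case could reach.

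**Conclusion.** The point holds as a minor defect of patient-safety wording in sections 5.13 and 7.2. It is a stated rule that gives a wrong result when followed, in two situations: any Group I woman withdrawn for pregnancy, and any patient with prior ACE-I therapy withdrawn for angioneurotic edema. Group II is untouched.

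Actual harm is unlikely because the treating nephrologists would probably step in. The primary endpoint, power and analysis are unaffected.

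The conclusion assumes that usual medication in Group I means the regimen in place before Measurement I, which is the plain reading of section 5.5. It also assumes that nothing in the unavailable appendices overrides the two sections. If the patient information does carry such an instruction, sections 5.13 and 7.2 would still need to be brought into line with it.

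**What to change.** Add the same exception to the exit sentence in sections 5.13 and 7.2: the participant goes back to usual medication, except that no ACE-I or AIIA is resumed after withdrawal for pregnancy and no ACE-I is resumed after angioneurotic edema. After withdrawal for another drug-related adverse effect, the treating nephrologist reassesses before an ACE-I or AIIA is resumed.

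The last clause leaves hyperkalemia, creatinine rises and similar cases to clinical judgement, without declaring resumption wrong. The cost is one amended sentence in each of two sections, with no extra patients, visits or procedures and no change to the analysis.
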